## 3. Discussion

UI is one of the chronic diseases that seriously affects middle-aged and elderly women in their quality of life. More and more women are suffering from UI. However, due to a lack of knowledge or willingness to seek medical treatment, many women, especially the elderly, develop moderate to severe UI before they visit a doctor for treatment. It has been recognized by the medical society that early detection is of great significance for the treatment of UI. Although a lot of risk factors are reported to be associated with UI, only some of these factors have been identified to reduce UI incidence and prevalence through their mitigation, which includes constipation, parity, gynecological diseases, or cardiovascular diseases [4,8]. UI prevalence and the likely associated factors have been widely reported by researchers from many countries. However, few studies have really focused on UI progress criteria and the factors that can potentially reverse UI, even slightly.

There are several studies on UI curation nowadays. A study by Zhishun Liu [19], a randomized controlled trial (RCT), showed that a greater than 50% decrease in terms of urinary leakage amount in SUI patients was achieved by treatment with electroacupuncture involving the lumbosacral region. A similar study by Renly Lim [28] on the curation of SUI reported a four-point ICIQ-SF score reduction in women with nonsurgical treatments for UI, which showed the minimum clinically important difference (MCID) with the baselines. A clinical study conducted by Liliana Giraldo-Rodríguez [9] on the epidemiology, progress, and predictive factors of UI in community-dwelling Mexican adults aged ≥ 50 indicated that depression and falls could decrease the incidence of UI, but they did not come up with criteria for UI curation or progress because of some limitations. In referring to the above studies, based on criteria for SUI disease curation, we thought backwards about one criterion of disease progress. We define “≥4 points of ICIQ-SF score increase” as one of the progress criteria for SUI progress, as it is more objective and convenient than the calculation of urine leakage or the frequency of urine leakage. The other criteria of SUI progress mainly adopt the Ingelman-Sundberg Indexing method. The criteria of UUI progress are defined by our team in consideration of the questionnaire of OABSS’s severity study on the UUI.

To date, there has been no published powerful clinical research on criteria for UI progress, suggesting that there is evidenced agreement on the risk-factors that can predict UI progress among the medical society. Meanwhile, there has been no research on disease progress models up to now, and the research on UI progress model is more meaningful for quality of life. Our work in this collaborative study aims to investigate the indicators most valuable for the prediction of UI development and progress through comparing the baseline and follow-up data for the same indicators, and, based on those data, by single factor and multi-factor Cox regression model analysis, we will try to develop a primary UI progress predication model for the world, which we believe will significantly contribute to the worldwide studies in this research area.

As screening for high-risk factors is mainly based on previous literature, many disease incidence prediction models are mainly based on questionnaires and basic gynecological examinations. The advantages of our study are that it includes morphology and ultrasound, electrophysiological examination, and other indicators that have rarely been performed. Those newly included indicators may provide early warning for UI progress and evidence for the early intervention and treatment of UI.

The UI predictive model will be developed to be an app compatible with mobile devices. When patients with symptoms of urine leakage enter relevant information and data via this app, the model system will automatically analyze their disease conditions to predict the potentiality of UI progress. It will serve to warm both the patients and the clinicians, remind the patients to seek medical treatments, and provide the clinicians evidence for preventive interventions. We believe that it could play an important role in alleviating the symptoms of urine leakage and promoting the recovery of UI.

The purpose for us recruiting patients from Beijing, a city in northern China, and Wuhan, a city in mid-southern China, is to ensure that the indicators and criteria could be determined from the analysis of the data from patients representing the northern and southern areas. If we succeed in the primary development of a predictive model for UI progress, the primary model should be applied in a large-scale study to demonstrate its effectiveness or to provide evidence for further modification.

Our study has some limits. Firstly, UI progress has not been clearly defined worldwide. The criteria for UI progress are defined by our team in referring a large amount of literature and the international recognized diagnostic criteria for UI and the questionnaire of ICIQ-SF and OABSS ’s study on UI. These criteria have been demonstrated to have certain clinical significance, but the relevant criteria for each of the indicators still need to be further discussed and explored in a large clinical sample research. Secondly, we design a convenient follow-up procedure via phone calls to reduce the drop-off rate. To avoid any possible information bias via phone calls, we trained the investigators before having them conduct the follow-ups, and will request patients who could not be diagnosed with progress to return to the hospital for follow-up confirmation. Thirdly, the progress years of UI are not clearly defined in the literature. Our study will project following the participants for up to 18 months, which is fine to observe UI progress, but is still not long enough to give powerful answers. We hope we can contribute towards a large-scale study in UI progress prediction through long-term follow-ups.

## 4. Conclusions

To the best of our knowledge, this is the first study to investigate the progress prediction model of associated risk factors for UI disease progress in elderly women. This study may provide more prediction information for elderly female UI patients and improve their quality of life. Information from this study could also be used to guide medical attention and to properly shape interventions for UI for older adults. The information regarding the problem of early diagnosis, treatment, and improvement of long-term prognosis among UI women is particularly useful, as there are few such studies in this UI progress area.

## Figures and Tables

**Figure 1 ijerph-19-00734-f001:**
[figure not shown]
Study flow chart.

**Table 1 ijerph-19-00734-t001:** Diagnosis criteria for subtypes of UI.

UI Types	Grade	Criteria
SUI grading	Mild	UI appears when coughing or sneezing without the need for a urinal pad
	Moderate	UI appears when running, jumping, or fast walking, and a urinal pad is needed
	Severe	UI appears when changing body position or resting at bed
UUI grading		According to OABSS indicators Question 3 (urgency) has a score of 2 or more, and the total score is 3 or more)
	Mild	3 ≤ score ≤ 5
	Moderate	6 ≤ score ≤ 11
	Severe	Score ≥ 12
MUI grading		According to the grade of SUI and UUI related symptoms, highest grading to be matched

UI: urinary incontinence; SUI: stress urinary incontinence; UUI: urgency urinary incontinence; MUI: mixed urinary incontinence; OABSS: overactive bladder symptom score.

**Table 2 ijerph-19-00734-t002:** Participant baseline screening, assessment, and follow-up schedule.

Characteristics	Baseline			Follow-Up (6 Months, 12 Months, 18 Months)		
	SUI	UUI	MUI	SUI	UUI	MUI
Age (≥60)	•	•	•			
Race	•	•	•			
Marital status	•	•	•			
Educational level	•	•	•			
Mainly physical labor	•	•	•			
BMI	•	•	•			
Parity	•	•	•			
Manner of delivery	•	•	•			
UI during pregnancy	•	•	•			
UI after childbirth	•	•	•			
Menopause	•	•	•			
Sex life	•	•	•			
Drink preference	•	•	•			
24-h Volume of liquid intake (mL)	•	•	•			
Smoking	•	•	•			
Comorbidities	•	•	•			
Chronic cough						
Asthma						
Diabetes						
Constipation						
Pelvic inflammatory disease	•	•	•			
Depression	•	•	•			
Urinary tract infection (last 4 weeks)	•	•	•			
History of gynecological surgery	•	•	•			
Family history of UI	•	•	•			
UI duration (year)	•	•	•	•	•	•
Frequency of urine leakage (time/month)	•	•	•	•	•	•
Symptoms accompaning urine leakage	•	•	•	•	•	•
Using urine pads (per/month)	▲	▲	▲	▲	▲	▲
Impact on life	•	•	•	•	•	•
POP-Q	•	•	•			
Hand test Oxford muscle strength grading	•	•	•			
One-hour urine pad test (g)	•	•	•			
Severity of UI	•	•	•	•	•	•
Mild						
Moderate						
Severe						
Pelvic floor electrophysiology examination	•	•	•			
Uroflowmetry	•	•	•			
Pelvic floor ultrasound	•	•	•			
Morphological examination	•	•	•			
ICIQ-SF score	•	•	•	•	•	•
OABSS score	•	•	•	•	•	•
UDI-6 score	•	•	•	•	•	•
UI progress				▲	▲	▲

•: Indicates mandatory items; ▲: Investigator will decide whether to perform the test according to clinical signs or clinical evaluation. UI: urinary incontinence; SUI: stress urinary incontinence; UUI: urgency urinary incontinence; MUI: mixed urinary incontinence; OABSS: overactive bladder symptom score; POP-Q: pelvic organ prolapse quantification; ICIQ-SF: International Consultation on Incontinence Questionnaire-short form; UDI-6: Urogenital Distress Inventory-6; BMI: body mass index.

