#### 2.2.1. Inclusion Criteria

Participants will be enrolled if they are: (1) ≥60 years of age; (2) educated enough to complete the questionnaires; (3) able to move freely to attend a hospital examination; (4) previously diagnosed as mild and moderate UI, including SUI, UUI, and MUI; (5) suffering urine leakage during occasional coughing, exertion, sneezing, fast walking, and other abdominal pressure; or (6) suffering frequent and urgent urination with urinary leakage and nocturia.

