#### 2.2.2. Exclusion Criteria

Patients will be excluded from the study if they were diagnosed as having: (1) severe pelvic organ prolapse, (2) serious cardiovascular and cerebrovascular diseases or other life-threatening diseases, (3) malignant tumor threatening patients life, (4) urogenital tract fistula, (5) previous history of anti-UI surgery and medication for UI, (6) no self-care ability and unable to complete the follow-up, and (7) severe UI and chronic urinary retention.

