After collecting the above-mentioned data, all participants will completed a gynecological examination, one-hour urinal pad test, pelvic floor electrophysiological examination, uroflowmetry, pelvic floor ultrasound, and morphological examination (Table 2). All the examinations will be conducted by the teams, using the same model instruments to avoid data biases, and data will be recorded on tablets connected to the database. The items to be inspected are as follows:(1)**Gynecological examination** includes uterus, vagina and appendages inspections; pressure inductive testing; bladder neck elevation testing; hand Oxford muscle strength classification testing; pelvic organ prolapse quantification (POP-Q); and one-hour urinal pad testing.(2)**UI questionnaires** concerning International Consultation on Incontinence Questionnaire-Short Form (ICIQ-SF) for investigation of UI frequency, degree, and its impacts on quality of life via 0–21 scoring to represent the severity of the UI [22]; OABSS questionnaire for assessment of the symptoms of the participants whose bladders are overactive and the severities of their urinary frequency, nocturia, urinary urgency, and urinary incontinence via scoring 0–15 to indicate the lowest to highest severity [23,24]; and Urogenital Distress Inventory-6(UDI-6) for evaluation of the lower urinary tract dysfunction via scoring 0–24 to present the severity of the urinary incontinence [25,26].(3)**Pelvic floor electrophysiological examination** on an instrument to collect data regarding indicators such as the maximum vaginal dynamic pressure, the vaginal resting pressure, the strength grades of type I and type II muscle, and the fatigue of type I and type II muscle fibers.(4)**Uroflowmetry** on the maximum and average rate of urine flow, urination time, and the urine flow curve.(5)**Pelvic floor ultrasound examination** performed by two attending doctors who have rich clinical experience of pelvic floor ultrasound for the residual urine, detrusor muscle thickness, bladder neck movement, urethral rotation angle, bladder posterior angle, the shape of the internal urethra opening, the distance from the lowest point of the bladder to the posterior lower edge of the pubic symphysis, levator ani muscle trauma, and levator ani hiatus area in the Valsalva status.(6)**Morphological examination** a study reported that the pelvis architecture was closely related to UI in women, especially pelvic inlet and pelvic outlet diameters as risk factors for UI [27], therefore, we include pelvic floor morphology into the study, which mainly includes the inclination angle of the sacrum and the anterior superior iliac spine, and the pelvic tendency.

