
Enrollment and participant grouping will be completed after all of the above procedures. Participant follow-up will be conducted for 6 months, 12 months, and 18 months from enrollment by investigators who were trained for each follow-up question. The follow-ups will be conducted by telephone to learn UI progress by inquiring participants’ symptoms in terms of the history of urinary incontinence, the frequency of urine leakage, the urinary syndrome, the usage of urinal pad, and conscious impact on life, and using a manner of questionnaires (ICIQ-SF, OABSS, and UDI- 6) (Table 2). Patients whose situation could not be confirmed as progressive or who struggle to express their symptoms will be requested to return back to the hospital for follow-up. Follow-up will be terminated for participants whose UI symptoms have aggravated upgrading. Rehabilitation guidance will be provided to participants in the termination of follow-up. Follow-up will be continued for participants with no symptom aggravation for no more than three calls in a period of no longer than 18 months.

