### 2.7. Study Endpoint

As there are no internationally accepted criteria for UI progress, we set up a series of criteria for referring literature, using the Ingelman-Sundberg Indexing method and International Continence Society [1] to judge UI progress in our study. The primary endpoint: UI progress will be judged if any of the following criteria are satisfied: For the SUI group, (1) urinary leakage inducive causes a change from coughing and sneezing to running, jumping and fast walking, or from running, jumping and fast walking to postural changes and rest at bed; (2) urinal pad usage changes from unneeded to needed; or (3) the baseline ICIQ-SF score is heightened for ≥4 [28]. For the UUI group, (1) OABSS score upgrades compared with the baseline, or (2) urinal pad usage changes from unneeded to needed. Progress will be confirmed for the MUI group if participants satisfy any of the progressive criteria for the SUI and UUI groups.

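### Recent urinary tract infection is recorded at baseline but not asked at the 6-, 12- and 18-month calls, so a passing infection can be recorded as lasting UI progress, mainly in the UUI and MUI groups

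*Protocol article*

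**What the plan says.** - **Schedule (Table 2).** The item "Urinary tract infection (last 4 weeks") is marked mandatory at baseline for SUI, UUI and MUI, and its three follow-up cells are blank. Leakage frequency, accompanying symptoms, ICIQ-SF, OABSS and UDI-6 are marked at both baseline and follow-up.
- **Content of the calls (section 2.6).** Investigators ask about "the history of urinary incontinence, the frequency of urine leakage, the urinary syndrome, the usage of urinal pad, and conscious impact on life" and administer ICIQ-SF, OABSS and UDI-6. Infection is not in the list.
- **Endpoint (section 2.7).** "UI progress will be judged if any of the following criteria are satisfied". In UUI it is enough that "OABSS score upgrades compared with the baseline" or that a pad becomes needed. In SUI the criteria are a more severe leakage trigger, new pad need, or an ICIQ-SF rise of at least 4. MUI progresses on any SUI or UUI criterion.
- **After an event (section 2.6).** Follow-up stops once symptoms have worsened. A hospital return is requested only when progress cannot be confirmed or the woman has difficulty describing her symptoms.
- **Elsewhere.** Infection does not appear in the inclusion or exclusion criteria (sections 2.2.1 and 2.2.2), in the grouping and grading rules, or in the examinations listed in section 2.6, which include no urine test.

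**The concern.** The 4-week window shows that the authors regard recent infection as relevant to current urinary symptoms. That relevance is the same whenever the symptoms are scored again, but the schedule drops the question at the contacts where the endpoint is judged.

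Section 2.6 describes OABSS as scoring frequency, nocturia, urgency and incontinence, which are symptoms an infection can produce for a short time. In UUI and MUI no minimum rise and no persistence are required, so a small temporary increase is enough. Because follow-up then ends, no later call can show recovery.

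What is at stake is outcome misclassification that may be related to the predictors. Residual urine, diabetes and baseline infection are all collected. Where such factors go with infection at a call, they could pass the univariate Cox screen in section 2.10 as predictors of UI progress when they partly predict infection. A larger sample does not remove a bias of this kind, and the model is meant for a patient-facing app (Discussion).

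**Working it through.** **1. The plan's own figure (section 2.9).** Inputs: 10–15 events per risk factor, about 10 factors (hence 100–150), 15–20% loss, and a training-to-validation ratio of 2:1.

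Formula: N = 100–150 ÷ (1 − loss) × 3/2. At 20% loss:
- 100 ÷ 0.80 = 125; × 1.5 = 187.5, rounded up to 188.
- 150 ÷ 0.80 = 187.5, rounded up to 188; × 1.5 = 282.

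The stated 188–282 reproduces. The present point does not alter it. It matters here because the 100–150 figure belongs to a study of 188–282 women, not 800.

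**2. The path from infection to event.**

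| Step | UUI and MUI | SUI |
|---|---|---|
| Infection asked at the call | No | No |
| What the infection must change | Any OABSS rise, or pad newly needed (MUI: also any SUI criterion) | Trigger, pad newly needed, or ICIQ-SF up by at least 4 |
| Re-test if a criterion is clearly met | None stated | None stated |
| Follow-up afterwards | Ends | Ends |

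**3. Possible size.** The documents give no infection rate, so both inputs are assumptions: u, the chance of an infection within 4 weeks of a call, 2–10%; and q, the chance that it causes a criterion to be met, 0.5. There are three calls (section 2.6), treated as independent.

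Cumulative false events = 1 − (1 − u × q)³
- Low: 1 − (1 − 0.02 × 0.5)³ = 1 − 0.99³ = 2.97%.
- High: 1 − (1 − 0.10 × 0.5)³ = 1 − 0.95³ = 14.26%.

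In women:
- 188 × 0.0297 ≈ 6 and 282 × 0.1426 ≈ 40.
- 800 × 0.0297 ≈ 24 and 800 × 0.1426 ≈ 114, before any loss.
- If all losses came before the first call: 800 × 0.80 × 0.0297 ≈ 19, up to 800 × 0.85 × 0.1426 ≈ 97.

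For fixed u and q these are upper figures, because a woman who would have progressed anyway is counted as false.

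**4. Effect of the group mix.** The Background puts SUI at 50% of UI cases. If that held in this convenience sample and no SUI woman were affected, the share would halve to about 1.5–7.1%. That is about 3–20 of 188–282, or 12–57 of 800. The truth lies between this and step 3 if q = 0.5 holds in UUI and MUI.

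**5. Sensitivity to q.** With q = 1 and u of 1%, 3%, 5% and 10%, the cumulative figure is 3.0%, 8.7%, 14.3% and 27.1%. The range is driven by inputs that the documents do not supply.

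**The case against.** The strongest reply is that the plan already has safeguards and that the baseline-only mark has an evident purpose.

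- **Infection as a predictor.** A reader might infer that the baseline item serves no purpose. The documents do not support that: it stands among the baseline characteristics and can enter the univariate Cox screen in section 2.10. Baseline infection in the model still does not correct an infection present at a later call.
- **Discretion and return visits.** A reader might infer that a woman with an infection is automatically recorded as progressed. She is not. Accompanying symptoms are asked at every call, UI progress carries the mark that leaves it to the investigator's clinical evaluation (Table 2 footnote), and unconfirmed cases return to hospital. These are real but partial safeguards. None prompts for infection, and a woman who clearly reports a higher OABSS is not an unconfirmed case.
- **Baseline scores.** A reader might go further and say that the plan sets false baselines or misplaces women in group or grade. Inclusion criterion 4 requires a previous diagnosis of mild or moderate UI, and what is done with a positive answer at the baseline visit is detail that a condensed article may leave to the full protocol. It is not shown to be a defect. The follow-up schedule differs, because Table 2 itself prints the item as baseline only.
- **Size.** It is tempting to set 114 false events against the 100–150 sought. That comparison mixes 800 women with a figure derived for 188–282.
- **Root cause.** Infection is one of several transient influences, and the absence of a minimum OABSS rise is the broader weakness. That stands. Infection is nevertheless the one for which the plan already has a question with a 4-week window.

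**Conclusion.** The point holds as a follow-up measurement gap. As printed, the schedule, the any-criterion endpoint and the end of follow-up together allow a transient infection to be recorded as lasting progress, chiefly in UUI and MUI. The gap can be read from the text and does not depend on an infection rate.

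Its size does. With 2–10% per call and half meeting a criterion, at most about 3–14% of women would have a false event over three calls, and fewer where SUI predominates or where the investigator recognises the infection. The low end is modest. The high end would matter to a model built on progress events. This is a cheap improvement to the outcome measurement and not an error in the sample size.

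**What to change.** 1. In Table 2, mark the existing 4-week infection item as mandatory at 6, 12 and 18 months in all three groups, and add it to the call content in section 2.6.
2. Where it is positive and a progress criterion is met, repeat the questionnaires once by telephone after the 4-week window, before recording progress and ending follow-up. If infection is still reported at the repeat, record the event with a flag, so that no woman, including one with recurrent infection, goes unjudged.
3. Allow for this repeat in section 2.6, which at present limits follow-up to three calls within 18 months.
4. Run a sensitivity analysis that excludes or censors infection-flagged events and excludes women positive at baseline, and compare the selected predictors and coefficients with the main model.

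**Cost.** One question per call. Under the assumptions above, infection-driven repeats would arise at about 1–5% of calls (0.02 × 0.5 to 0.10 × 0.5), plus repeats for true progression that coincides with infection. A few event dates fall about a month late, and some true progression reported alongside infection is confirmed later. Self-reported infection overlaps with worsening urgency, which is why the repeat is limited to one and the flagged event is kept.
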